### Procedure

Eligible stroke survivors will be initially approached while they are an inpatient by a local researcher, who will provide verbal and written information about the trial before seeking informed consent. Examples of an information sheet and informed consent form for stroke survivor participants are provided in online supplemental appendices 2–4.

10.1136/bmjopen-2023-074607.supp2Supplementary data

10.1136/bmjopen-2023-074607.supp3Supplementary data

10.1136/bmjopen-2023-074607.supp4Supplementary data

To ensure that the trial population is representative of the clinical stroke population and inclusive of stroke survivors with cognitive impairment (including comprehension or language difficulties), recruitment procedures will include the use of accessible materials and procedures for consultee declaration (where appropriate), in compliance with the Mental Capacity Act 2005 (MCA).^44^ As per the MCA, each stroke survivor will be assumed to have capacity unless it is established that they lack capacity. If there is any concern about capacity the local researcher will consult ward staff and/or a family member/carer (as appropriate) and a collective decision will be made as to whether the stroke survivor is deemed to have capacity to consent to participation in the trial. Changes in capacity will be monitored throughout the trial.

Potential stroke survivor participants who are deemed to have capacity to consent will be provided with written and verbal information about what their participation in the study would involve. Following time to consider participation (including discussion with family and/or health professionals), those wishing to take part will provide informed consent through signing (or making a mark), or if they are unable, through witnessed verbal consent (by an independent observer). Should a potential participant be discharged prior to consent being gained and they consent to being contacted by the researcher, consent procedures will take place in their own home.

Should stroke survivors be deemed to lack capacity to provide informed consent, the researcher will seek to identify ‘a supporting family member, friend or carer’ (defined as someone who is in regular (at least weekly) contact with the stroke survivor), to support intervention delivery and outcome assessment. This individual will not necessarily be enrolled in the study themselves, unless they choose to enrol as a carer participant. If such a supporter is identified, the local researcher will either: act in accordance with an advance directive relative to research participation (if available) or seek advice from a personal consultee (through consultee declaration). If a personal consultee is approached, they will be provided with an additional information sheet outlining their role. Consultees will provide assent in person or via telephone (and signed by the local researcher, eg, if the consultee is unable to visit the hospital prior to the stroke survivor’s discharge). Carer participants will be approached by the local researcher once stroke survivors with capacity have given their verbal agreement or following provision of a consultee declaration for a stroke survivor participant who lacks capacity. Those wishing to participate will be asked to provide informed consent using the same procedure described above. Carers lacking the capacity to provide written informed consent will be excluded.

The local researcher will administer baseline questionnaires to stroke survivor and carer participants face-to-face and offer support where required. Proxy completion of questionnaires by a carer, family member or friend will be permitted (for those with and without capacity), with separate proxy questionnaires provided if required. Stroke survivors will also be asked to continuously wear an activPAL activity monitor on the thigh of their strongest/unaffected leg for 9 consecutive days. The monitor will be attached by the local researcher. They will also be asked to complete a purposely developed daily diary. This will capture if/when the monitor has been removed; the time they went to bed and got up each day and whether they had episodes of sleep (ie, naps) during the day. This information will assist with analysis and facilitate monitoring of adverse reactions to the materials used to attach the monitor. Local researchers will also collect data on risk markers for cardiovascular disease through face-to-face assessment or retrieval from medical records. These include height and weight (for calculation of BMI), waist circumference and BP.

At the follow-up time points (6, 12 and 24 months post-registration), participant-completed outcome assessments will be administered by post in an assessment pack, including a covering letter and a prepaid envelope for postal return. Activity monitors may be administered face-to-face by a local researcher or alternatively, be sent by post to the participant and returned via prepaid envelope. Cardiovascular risk markers (with the exception of height) will be collected alongside the activity monitor assessment. If it is not possible to organise a face-to-face visit, with the participants’ agreement, options for self-assessment will be explored. Guidance will be provided to local researchers as to the action required if a BP reading is abnormal, including reporting this to a named clinician or notifying the participant’s general practitioner (GP). The participant will also be encouraged to discuss this with their GP.

At each participant follow-up, changes in circumstances, including change of address, institutionalisation and death will be obtained from either recruiting teams, healthcare providers, participants or their relatives. Additionally, for stroke survivors, the following data will be collected from electronic health records via routine data providers or directly from the recruiting hospital at each time point: total major vascular events (composite of non-fatal stroke; non-fatal myocardial infarction; or death due to any vascular cause (including unexplained sudden death));^39^ death; hospital admissions; emergency department attendance and institutionalisation. Stroke survivors will be made aware of the use of routine data providers (including NHS England, SystmOne, EMIS Web and other relevant providers) at the time of study entry.

The study timeline for participants is presented in figure 1.

**Figure 1 F1:**
[figure not shown]
Study timeline for participants.

Initial letters, reminder letters and a participant pathway diagram will be distributed to participants to maximise data return at all time points. The questionnaire sent to assess intervention compliance at 12 weeks post-hospital discharge will also serve as a reminder of study participation and act as a retention tool. At the follow-up time points, reminders will be administered via telephone, text message, email or post (according to participant preference) should the questionnaire not be returned within 2 weeks. If outcome assessments (with particular emphasis on the NEADL as the primary outcome), cannot be obtained by post, then (where appropriate) the assessments may be administered over the telephone or face-to-face to maximise return of data. Missing data, except individual data items collected via the postal assessment packs, will be sought until: it is received; confirmed as not available; or the trial is at analysis.

In instances where a participant withdraws from the trial clarification will be sought as to whether this is from all trial activities or individual components, for example, wearing the activity monitor or consenting to be contacted about participation in process evaluation activities. Unless participants explicitly instruct otherwise, electronic health record data will continue to be collected.

### Data management

Data will be monitored for quality and completeness using established verification, validation and checking processes, for example, double data entry, and securely stored. Received activPAL data will be subject to quality checks by researchers and where needed, additional details to aid interpretation will be sought from the recruiting site and/or participant diaries. All data collected during the course of the trial will be kept strictly confidential using established processes. Data will be securely archived for 10 years after the completion of the study and then destroyed.

### Statistical analysis

All analyses and data summaries will be conducted on the intention-to-treat population (ITT),^45^ defined as all participants registered to the trial, regardless of non-compliance with the protocol or withdrawal from the study or losses to follow-up. Data from all participants recruited within a stroke service will be analysed according to the randomised allocation for that stroke service. No formal interim or subgroup analyses are planned, and final analysis will take place when all available data have been received.

#### Sample size

As previously described, our original plan for a large definitive multicentre RCT was reduced in size and scope, due to issues related to the COVID-19 pandemic. We aim to recruit 300–400 participants across 15 stroke services. This revised sample size is based on the anticipated recruitment rate within the remaining time available in the funded programme, estimated at two participants per month per site. As intervention effectiveness will not be evaluated and all analyses will be of an exploratory nature, the study does not have a formal power calculation.

#### Primary endpoint analysis

In line with study objectives, all endpoint analyses will be exploratory and provide preliminary estimates of intervention effect. The primary outcome will be compared between randomised groups using multilevel mixed effects model^46^ adjusting for design effects and other relevant known predictors of outcome, with participants nested within services, with services treated as random effects. If appropriate, missing data will be multiply imputed at the individual participant level. Parameter estimates will be reported with 95% CIs. Sensitivity analyses of the primary endpoint will be conducted to assess the impact of missing data, the choice of imputation model and of assuming data are missing not at random, as appropriate. For the primary analysis, missing data will be assumed missing at random.

#### Incorporating the SWAT into the statistical analysis

For the primary analysis, the SWAT intervention will be accounted for in the regression model using an interaction term. Sensitivity analyses will explore the impact of the SWAT on the Get Set Go intervention effect, for example, analysing the outcomes as a three-arm study separating the two SWAT arms. This will be described in further detail in the statistical analysis plan.

#### Secondary endpoints analyses

Secondary outcomes will be analysed in a similar manner to the primary outcome. For secondary outcomes, summary statistics will be presented for each time point by treatment group (means, SD, medians, minimum, maximum and quartiles for continuous variables, and counts and percentages for categorical variables). Secondary outcomes will be analysed using the same approach as the primary outcome with the relevant model for the type of outcome variable using multilevel linear or logistic regression, with multiple imputation for missing data where appropriate. Continuous distributions will be transformed where residuals are non-normal.

Self-reported falls, institutionalisation, readmission, cardiovascular risk markers, total major vascular events and death rates between treatment arms will be summarised descriptively.

Quantitative summaries of intervention delivery will evaluate uptake of the intervention, adherence to the processes, staff and participant engagement and quality of intervention delivery, overall and by each site. Data on usual care will be summarised descriptively.

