### Objectives

The primary objective is to undertake a preliminary exploration of whether the intervention (Get Set Go) is likely to improve the ability to complete extended activities of daily living (EADLs) in the first year after stroke. A key secondary objective is to explore whether the intervention is likely to reduce sedentary behaviour. Other secondary objectives are to:

Explore core resource use and costs associated with delivering the intervention including impacts on wider care.Explore whether the intervention reduces cardiovascular risk factors.Explore whether the intervention reduces disability.Explore whether the intervention improves health and well-being outcomes, such as health-related quality of life and mental well-being.Explore whether the intervention reduces carer strain.Explore and understand implementation of the intervention, including intervention adherence, compliance, the process, benefits and challenges.Explore and understand how the intervention is experienced and understood by recipients and providers.Explore potential moderators and mediators of the intervention effect.

Objectives 1−5 will be addressed in the cRCT. Additional objectives addressed in the cRCT relate to gathering feasibility and acceptability data to inform future trial designs in stroke rehabilitation. Objectives 6−8 will be addressed in an embedded mixed-methods process evaluation (protocol reported separately), which will develop an understanding of how the intervention is implemented, understood and experienced by both providers and recipients.

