### Endpoints

The primary endpoint is stroke survivor self-reported EADLs at 12 months post-registration. The key secondary endpoint is mean daily sedentary time (minutes) at 12 months post-registration using activity monitor (activPAL) data, which provides a valid measure of posture and transitions in people with impaired mobility.^26^ Other secondary endpoints at 6, 12 and 24 months post-registration (unless stated otherwise) for stroke survivor participants are listed below:

Sedentary behaviour measured by activity monitor.EADLs (at 6 and 24 months only) measured by Nottingham Extended Activities of Daily Living scale (NEADL).^27^
Health and disability measured by WHO Disability Assessment Schedule 2.0 (12-item).^28–32^
Mental well-being measured by Warwick-Edinburgh Mental Well-being Scale.^33^
Health status measured by European Quality of Life 5-Dimension Health Questionnaire (5 levels; EQ-5D-5L).^34^
Quality-adjusted life year (QALY) gains (as above).Fatigue as measured by Fatigue Assessment Scale.^35 36^
Death.Falls and use of a walking aid (12 weeks post-discharge, and at 6, 12 and 24 months).Self-reported sedentary behaviour measured by the Measure of Older Adults’ Sedentary Time^37^ and a Sedentary Behaviour Visual Analogue Scale (adapted from Chastin *et al*, 2019^38^).Institutionalisation, hospital readmission and emergency department attendance rates.Cardiovascular risk markers: Body mass index (BMI), waist circumference, blood pressure (BP).Total major vascular events: Composite measure of non-fatal stroke, non-fatal myocardial infarction or death due to any vascular cause (including unexplained sudden death).^39^
Self-reported health and social care service use and informal care inputs measured by a Client Services Receipt Inventory (CSRI) specifically adapted for this trial from versions used in previous stroke rehabilitation trials.^40 41^
Costs from a health and social care perspective, and a societal perspective that further includes informal care.

The carer endpoint is caregiver burden measured by Modified Caregiver Strain Index^42^ at 6, 12 and 24 months.

An overview of which assessments are undertaken at each time point and the method of completion is provided in table 3. Information about the validity and reliability of the measures used is available in online supplemental appendix 1. Stroke survivors will also complete an additional brief postal questionnaire at 12 weeks post-discharge.

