10.1136/bmjopen-2023-074607.supp1Supplementary data

**Table 3 T3:** Overview of assessments and method of completion at each study time point

Outcome/assessment	Method of completion	Time point			
		Baseline	6 months post-registration	12 months post-registration	24 months post-registration
Stroke survivor					
Demographic details	Self-report	X			
Nottingham Extended Activities of Daily Living Scale^27^	Self-report	X	X	X	X
WHO Disability Assessment Scale 2.0 12-item^28–32^	Self-report	X	X	X	X
Warwick-Edinburgh Mental Well-being Scale^33^	Self-report	X	X	X	X
European Quality of Life 5-Dimension Health Questionnaire^34^	Self-report	X	X	X	X
Fatigue Assessment Scale^35 36^	Self-report	X	X	X	X
Measure of Older Adults’ Sedentary Time^37^	Self-report	X	X	X	X
Sedentary Behaviour Visual Analogue Scale (adapted from 38)	Self-report	X	X	X	X
Use of a walking aid	Self-report	X	X	X	X
Falls question	Self-report	X	X	X	X
Hospital admissions	Self-report/electronic health records		X	X	X
Client Service Receipt Inventories to collect data on health and social care use and informal care inputs (adapted from 40 41)	Self-report	X	X	X	X
Total major vascular events^39^	Electronic health records via routine data providers	X	X	X	X
Sedentary behaviour—activPAL measurements	Researcher administration/post	X	X	X	X
Risk markers for cardiovascular disease (height* and weight for body mass index; waist circumference; blood pressure) *Collected at baseline only	Researcher collection from notes/researcher visit/self-completion	X	X	X	X
Adverse events	Self-report/electronic health records		X	X	X
Survival status	Researcher collection from electronic health records		X	X	X
Admission to institution	Self-report		X	X	X
Carer					
Demographic details	Self-report	X	(X)	(X)	(X)
Modified Caregiver Strain Index^42^	Self-report		X	X	X
Employment/occupation status	Self-report	X	X	X	X

(X) only collected if ‘new carer’.

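### BMI, waist circumference and blood pressure are only to be described, although an objective and the general analysis statement call for an effect estimate with an interval

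*Protocol article*

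**What the plan says.** The Objectives section lists, second among the other secondary objectives: "Explore whether the intervention reduces cardiovascular risk factors". It then says where this will be answered: "Objectives 1−5 will be addressed in the cRCT".

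The Endpoints section names BMI, waist circumference and blood pressure as secondary endpoints at 6, 12 and 24 months. Table 3 shows them at baseline as well, and the Procedure section describes that baseline collection: "Local researchers will also collect data on risk markers for cardiovascular disease through face-to-face assessment or retrieval from medical records".

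The Primary endpoint analysis section commits every endpoint analysis to giving an exploratory, preliminary estimate of the intervention's effect.

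The Secondary endpoints analyses section opens with a general rule, "Secondary outcomes will be analysed in a similar manner to the primary outcome", and repeats it with the model family, multilevel linear or logistic regression: "Secondary outcomes will be analysed using the same approach as the primary outcome with the relevant model for the type of outcome variable". A later paragraph of the same section takes a named list out of that rule: "Self-reported falls, institutionalisation, readmission, cardiovascular risk markers, total major vascular events and death rates between treatment arms will be summarised descriptively".

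**The concern.** The markers are continuous and have a baseline value, like the other continuous outcomes that the protocol sends to a multilevel linear model. They are tied to an objective that the cluster trial undertakes to address. Yet they sit in a list whose other members are all event outcomes, and no reason is given for treating them differently.

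What is lost is the adjusted between-arm difference and its interval. With about 15 randomised services, chance imbalance in baseline blood pressure or weight between arms is quite possible, and an unadjusted difference in follow-up means carries it forward. A reader who wants a sense of precision would have to build an interval from the published means and SDs. The obvious way of doing so treats participants as independent.

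**Working it through.** **Text check.** The protocol states no power calculation, SD or ICC, so there is no figure of its own to reproduce. The first check is to set the sections side by side.

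1. Objective: explore an effect on cardiovascular risk factors, within the cluster trial (Objectives).
2. Endpoint: BMI, waist circumference and blood pressure at 6, 12 and 24 months (Endpoints), plus baseline (Table 3, Procedure).
3. General commitment: every endpoint analysis gives a preliminary effect estimate (Primary endpoint analysis).
4. Specific rule: descriptive summary only (Secondary endpoints analyses).
5. No other section gives these markers a model, an effect estimate or an interval.

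If item 4 is an exception to the general rule, which is the natural reading, then items 1 and 3 are not met for these markers. If it is not an exception, two paragraphs of the same section disagree. Either way the text needs an edit. The point is not an omission left to the analysis plan, because the article names the markers and fixes their analysis.

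**Would an estimate be feasible, and how far off is the crude alternative?**

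Inputs from the protocol: 300–400 participants, 15 services, 1:1 allocation by service. Assumptions: an 8:7 split, equal service sizes, ICC 0.01–0.05, retention 70–100%, and all participants counted as stroke survivors.

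- Participants per service with data: m = N × retention / 15
- Design effect: DE = 1 + (m − 1) × ICC
- Cluster-adjusted half-width in SD units: t(0.975, 13 df) × √[DE × (1/n1 + 1/n2)], with n1 = 8m and n2 = 7m
- Half-width ignoring clustering: 1.96 × √(1/n1 + 1/n2)

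Worked case, N = 300, full retention, ICC 0.05: m = 20; DE = 1 + 19 × 0.05 = 1.95; n1 = 160, n2 = 140; √(1/160 + 1/140) = 0.1157. Ignoring clustering: 1.96 × 0.1157 = 0.227. Cluster-adjusted: 2.160 × √1.95 × 0.1157 = 0.349.

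| N | Retention | m | Half-width ignoring clustering (SD) | Cluster-adjusted half-width, ICC 0.01 to 0.05 (SD) |
|---|---|---|---|---|
| 300 | 100% | 20.0 | 0.227 | 0.273 to 0.349 |
| 300 | 70% | 14.0 | 0.271 | 0.318 to 0.384 |
| 400 | 100% | 26.7 | 0.196 | 0.243 to 0.327 |
| 400 | 70% | 18.7 | 0.235 | 0.281 to 0.355 |

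The adjusted interval is wider by a factor of 1.17 (0.318/0.271) to 1.67 (0.327/0.196). Of this, 2.160/1.96 = 1.10 comes from using 13 degrees of freedom and the rest from the design effect.

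The Recruitment section counts stroke survivors and carers together, so the number of survivors may fall below 300. With an assumed 200 survivors the cluster-adjusted half-width is 0.325 to 0.436 SD over the same ranges.

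These figures do not include any gain from baseline adjustment. The protocol gives no baseline-to-follow-up correlation from which to size that gain.

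**The case against.** The strongest reply is that this is an external pilot. The objective is to explore, the Sample size section says effectiveness will not be evaluated, and describing lower-tier outcomes in an unpowered study is reasonable restraint. A general rule followed by a named exception is also ordinary drafting. Measurement is a further argument: Table 3 allows the markers to come from notes, a researcher visit or self-completion, so a baseline value from the records may be paired with a self-measured follow-up value, which makes a baseline-adjusted model less clean.

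Part of this stands. Pilot status rules out confirmatory claims and lowers the weight of the point. It does not explain the exception, because the same pilot models its other continuous secondary outcomes. Mixed measurement modes call for caution in interpretation, but they affect raw arm means too, and the article does not offer them as its reason.

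A reader might infer three stronger things that the documents do not support:

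- *That the objective cannot be answered at all.* Summaries are given by arm at each time point, so a crude contrast is available, and the objective is exploratory.
- *That the reported SDs understate uncertainty.* An SD describes spread between participants and makes no claim about the precision of an arm difference. Only a standard error or interval derived from it without allowing for clustering would be too small, and the plan reports neither.
- *That falls must also be modelled.* No listed objective names falls, so the mismatch between objective and analysis does not reach them.

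**Conclusion.** The point holds in a limited form. The article assigns three continuous, baseline-measured markers to descriptive summary. That leaves an objective it undertakes to address, and its commitment on all endpoint analyses, without an adjusted estimate or interval for those markers. The primary and key secondary endpoints are not affected.

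A proper estimate is feasible at the planned size but would be imprecise: a 95% CI half-width of about 0.27–0.38 SD with 300 survivors and 0.24–0.36 SD with 400. An interval that ignored clustering would be about 0.20–0.27 SD. These sizes rest on the assumed ICC, retention, equal service sizes and 8:7 split. The textual mismatch rests on none of them. The analysis plan is not shown and may already resolve it, but the article as written should be put right.

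**What to change.** Remove BMI, waist circumference and blood pressure from the descriptive list. Analyse them with the multilevel linear model already specified for the other continuous secondary outcomes, adjusted for the baseline value of the marker. Report the exploratory adjusted difference with its 95% CI at 6, 12 and 24 months where data allow. The 24-month data will be partial: recruitment is projected to end in April 2023 and follow-up in April 2024, so the latest recruits reach only about 12 months.

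Report how each measurement was obtained (notes, visit or self-completion) by arm and time point, and interpret the estimates with that in mind. Falls and the other event outcomes may stay descriptive.

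If the sponsor prefers to keep the markers descriptive, the alternative is to reword the objective accordingly and limit the statement about all endpoint analyses.

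The cost is one changed sentence and a few extra models on data already being collected. If systolic and diastolic pressure are analysed separately, that is at most 4 markers × 3 time points = 12 differences. The intervals will be wide, and with that many contrasts they should be presented as exploratory estimates and not as tests.

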### Strategies to improve intervention adherence

The implementation team will maintain regular contact with clinical leads in sites allocated to the intervention arm to monitor delivery of the intervention and provide support as required. Clinical staff who are responsible for delivering the intervention will also complete monitoring records for all stroke survivors (whether or not they are trial participants) to document whether key tasks relating to the intervention have been completed (no personal data will be recorded for non-trial participants). It will be advised that a nominated member of staff checks these records have been completed on a regular basis (eg, towards the end of each shift). Regular review of these records will enable the study team to monitor intervention adherence and provide insight into intervention delivery. A short postal questionnaire completed by stroke survivor trial participants at 12 weeks post-hospital discharge will also assess intervention compliance, with those in the intervention arm responding to questions about the intervention; all participants will be asked about falls and use of a walking aid. Data on compliance will be analysed using descriptive summary statistics by allocation. Finally, intervention fidelity will be explored separately within the process evaluation, through site-based observations of intervention delivery, interviews with those delivering and receiving the intervention and documentary analysis (including completed intervention materials).

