### Adverse event reporting and harms

Adverse events (AEs) such as falls and musculoskeletal injuries represent an inherent consequence of an active rehabilitation process and therefore cannot be entirely avoided. Similarly, in this patient population, acute illness resulting in hospitalisation, new medical problems and deterioration of existing medical problems are expected. In recognition of this, events fulfilling the definition of an AE or SAE will not be reportable in this study unless they result from administration of any research procedures and therefore fulfil the definition of an unexpected and related SAE, or if they constitute one of the following: death, hospital readmission, institutionalisation, treatment on an emergency outpatient basis or emergency department attendance. The latter will be reported at 6, 12 and 24 months post-registration follow-up by the clinical research team using health and social care records. All related/unexpected SAEs occurring from the date of consent up to 24 months post-registration must be reported within 24 hours of the clinical research staff becoming aware of the event. All related/unexpected SAEs will be reviewed by the CI and subject to expedited reporting to the sponsor and the main Research Ethics Committee (REC) by the CTRU on behalf of the CI within 15 days.

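### Self-reported falls are summarised by arm only, with no planned cluster-adjusted difference or confidence interval, although the model for binary secondary outcomes is already in the plan

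*Protocol article*

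**What the plan says.** All references are to the protocol article.

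- **Collection.** Endpoints lists "Falls and use of a walking aid (12 weeks post-discharge, and at 6, 12 and 24 months" as a secondary endpoint. Strategies to improve intervention adherence says of the 12-week questionnaire that "all participants will be asked about falls and use of a walking aid". Table 3 adds a falls question at baseline.
- **Event reporting.** Adverse event reporting and harms says "Adverse events (AEs) such as falls and musculoskeletal injuries represent an inherent consequence of an active rehabilitation process". It then states that "events fulfilling the definition of an AE or SAE will not be reportable in this study unless they result from administration of any research procedures". Such an event must also count as an unexpected and related SAE. The other exceptions are these: "death, hospital readmission, institutionalisation, treatment on an emergency outpatient basis or emergency department attendance".
- **Analysis.** Secondary endpoints analyses first gives a general rule: secondary outcomes follow the primary outcome's approach, with multilevel linear or logistic regression, and "summary statistics will be presented for each time point by treatment group". The next paragraph takes a list of outcomes out of that rule: "Self-reported falls, institutionalisation, readmission, cardiovascular risk markers, total major vascular events and death rates between treatment arms will be summarised descriptively".
- **Status.** Primary endpoint analysis says "all endpoint analyses will be exploratory and provide preliminary estimates of intervention effect", and that parameter estimates come with 95% CIs.

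**The concern.** Get Set Go asks staff to encourage stroke survivors to stand and move more, and people who need light manual contact from one person to avoid falling on standing are eligible. The protocol itself names falls as an expected consequence of active rehabilitation. A future trial will therefore want to know from this pilot how large an increase in falls has not been ruled out.

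For falls without a serious consequence, the self-report item carries that information alone, and it is one of the outcomes left unmodelled. Counts and percentages from two groups of seven or eight services carry no measure of uncertainty. A reader who supplies one informally is likely to treat participants as independent. The benefit outcomes analysed under the general rule get a model that accounts for service; this harm outcome does not.

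**Working it through.** **1. Route of a fall into the data.** A fall followed by death, readmission, institutionalisation or emergency care is reportable as that event. A fall without such a consequence is not reportable unless it arises from a research procedure and meets the definition of an unexpected and related SAE. What remains is the self-report falls question, asked in both arms at 12 weeks post-discharge and at 6, 12 and 24 months.

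**2. What the planned summary delivers.** For a categorical outcome it gives counts and percentages by arm at each time point. A raw difference can be read off. No adjusted difference and no interval is planned for falls.

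**3. What an interval would look like.** The plan states no precision or power figure for falls, and Sample size says there is no formal power calculation, so there is nothing to reproduce. The following is an illustration.

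From the documents: N = 300-400, 15 services, 1:1 allocation of services, hence 7 v 8.

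Assumed: proportion reporting a fall p = 0.30-0.45, service ICC = 0.01-0.05, return = 75-85%, equal service sizes.

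Formulas:
- m = N × return / 15; n1 = 7m; n2 = 8m
- design effect DE = 1 + (m − 1) × ICC
- SE = √[p(1 − p)(1/n1 + 1/n2) × DE]
- half-width = t(13 df) × SE, with t = 2.160
- for comparison, independent participants: 1.96 × SE with DE = 1

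Narrowest case (N = 400, return 85%, p = 0.30, ICC = 0.01):
- m = 340/15 = 22.67; n1 = 158.7; n2 = 181.3
- DE = 1 + 21.67 × 0.01 = 1.217
- SE = √[0.21 × (1/158.7 + 1/181.3) × 1.217] = 0.0549
- half-width = 2.160 × 0.0549 = 0.119

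Widest case (N = 300, return 75%, p = 0.45, ICC = 0.05):
- m = 225/15 = 15; n1 = 105; n2 = 120
- DE = 1 + 14 × 0.05 = 1.70
- SE = √[0.2475 × (1/105 + 1/120) × 1.70] = 0.0867
- half-width = 2.160 × 0.0867 = 0.187

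| Reading of the arm difference | 95% half-width, percentage points |
|---|---|
| Allowing for service | 11.9 to 18.7 |
| Treating participants as independent | 9.8 to 13.0 |

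Within the same scenario the ratio runs from 1.18 to 1.59.

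**4. Direction of the uncertainty.** The Abstract and Recruitment count carers within the 300-400. If fewer than 300-400 stroke survivors are recruited, the intervals are wider than shown.

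**The case against.** The strongest reply is that this is an external pilot, not powered and not meant to evaluate effectiveness, and that descriptive harm summaries are a defensible choice in such a trial. Falls are asked about in a structured way in both arms, which is a reasonable alternative to ad hoc event forms. Participants are not blinded, so a modelled difference may carry reporting bias that a service random effect cannot remove. An interval of this width would leave substantial harm and substantial benefit both possible. All of that stands, and it limits the weight of the point. It argues against a significance test, but not against an interval: the plan already commits to exploratory estimates with 95% CIs for an unpowered primary outcome.

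Three stronger readings are tempting, and the document does not support them.

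- *A reader might infer that the pilot gives no between-arm information on harm.* It does: falls are tabulated by arm at each time point. Falls with serious consequences surface as reportable events, Table 3 also has an adverse-events row at 6, 12 and 24 months, and the Programme Steering Committee monitors safety. Nor does the document rank falls as the main harm; it names them together with musculoskeletal injuries.
- *A reader might infer a contradiction with the statement that all endpoint analyses provide preliminary estimates of effect.* That sentence sits under the primary endpoint and mainly describes the status of the analyses. The descriptive list reads as a specific exception to a general rule, and an analyst would know what to do with falls.
- *A reader might take the 1.2 to 1.6 ratio as an error in the plan.* The plan never proposes an interval that ignores clustering. The ratio shows only what happens if a reader calculates one from the raw percentages.

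**Conclusion.** The point holds as a modest reporting weakness. The only systematic record of falls without serious consequences is confined to a descriptive summary by arm, while a suitable model is already planned for other binary secondary outcomes. The by-arm percentages permit a crude comparison but do not show what excess in falls the data leave open. Under the stated assumptions that uncertainty is about ±12 to ±19 percentage points. The range depends wholly on the assumed fall proportion, ICC and return, none of which the document gives. The conclusion that no adjusted difference or interval is planned for falls rests on the protocol text and not on those assumptions. The analysis plan is not shown and could add the interval, but the protocol as written assigns falls to the descriptive list.

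**What to change.** In Secondary endpoints analyses, move self-reported falls from the descriptive-only list to the multilevel logistic model already planned for binary secondary outcomes.

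- Include arm, a random effect for service and the minimisation factors (SSNAP grade, service composition, unit size).
- Adjust for the baseline falls item only if its recall period precedes the admission; the article does not give that period.
- Report the arm difference with its 95% CI and no significance test at 12 weeks post-discharge, 6 months and 12 months. The 24-month summary can stay descriptive: recruitment runs to the end of April 2023 and follow-up ends in April 2024, so later recruits cannot reach that time point.
- Label the result an exploratory safety estimate, and state that falls are self-reported by unblinded participants.
- Leave death and major vascular events descriptive.

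The cost is a change of wording in the analysis plan and one extra model per time point, with no new data. The downside is wide intervals, which must be reported and not read as evidence that falls are unaffected.
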